**Figure 3 Fig3:**

**Times schedule.**

### Experimental procedure

1. Preparation phase: During the preparation phase of 35 minutes, participants are asked to dispense the first saliva sample, to run the emotion recognition task (*decode*_*EMO*), to put on the ECG belt to assess HR, to fill in the sociodemographic questionnaire ([name] et al. 2007) and self-report measures of body image, affect and eating behavior (*pre media exposure*).

Assessment of biological measures: Measurement of salivary cortisol and alpha-amylase concentrations during and after media exposure will be performed 9 times. The sampling protocol was chosen to capture peak and recovery of salivary alpha-amylase, as well as salivary cortisol (Kirschbaum & Hellhammer 1989; Nater & Rohleder 2009). The participants will be instructed to place the cotton roll in a specific area of the mouth for 2 minutes and chew on it and to avoid physical exercise, eating or drinking anything but water, brushing teeth or smoking for at least 1 hour before examination. Medication, somatic and mental diseases, date of last menstruation, last alcohol consumption and habitual smoking will be documented. HR will be measured continuously using ambulatory monitoring systems such as Movisens (www.movisens.com). Belts will be put on at the beginning of the experimental procedure and will be worn during the whole procedure. To minimize artifacts (e.g. orthostatic reaction) we analyze HR as well as HRV after a rest of two minutes after changing the position (e.g. going from room 2 into room 3). Start and end points of different stages of the experiment will be marked using corresponding software.

Assessment of emotion recognition: The emotion recognition task, which is part of the multilevel assessment of ER capacity, is based on a computerized assessment determining the *quantity* of information that is necessary to each individual observer to achieve effective decoding of a facial expression of emotion (*decode*_*EMO*) (Miellet et al. 2011). The example (Figure 4) illustrates how phase-coherence of the very same individual (image) depicting a Westerner posing with a neutral expression is manipulated. The approach is coupled with QUEST (Watson & Pelli 1983), a psychometric method that allows the rapid estimation of a psychophysical threshold. Altogether 20 male and 20 female faces from the Karolinska Directed Emotional Faces (KDEF) face database (Lundqvist et al. 1998), displaying the 6 facial expressions (i.e., happy, sad, fear, anger, surprise, disgust) plus neutral are used.


**Figure 5 Fig5:**
[figure not shown]
**Experimental procedure.**

Manipulation check: The implicit picture recognition test at the end is a custom script written in MatLab, using the Psychophysics Toolbox extensions (Brainard 1997; Pelli 1997). Subjects have to judge whether they have previously seen the picture by use of two keys on a standard keyboard. In both conditions, subjects are presented with ten images from the magazine used in the media exposure and ten randomly selected images from similar magazines. Pictures are presented until a response is given to ensure full recognition and encoding (reaction time; see (Grill-Spector & Kanwisher 2005)) and hit rate (%-correct recognition) as well as d’ (a measure for sensitivity) are used to calculate subject’s performance. At the end of the experiment BMI is measured, the HR belt is removed and the 9th salvia sample is collected. A short relaxation session is offered where necessary.

### Disclosure and debriefing

At pretreatment, participants are informed that they participate in a study investigating psychological well-being and psychophysiological responses to daily stressors in young women. After the experiment, they are asked not to disclose the purpose of the study to potential participants. They will be debriefed 3 months later, after the second performance of the experiment and receive a summary of the overall study aim together with preliminary findings as well as an overview of the results of their personal data entries.

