### Methodological aspects

#### Power analysis

Sample size calculations are based on findings of small to medium effects of mass media engagement on body image in young adults from the general population (Levine & Murnen 2009) and based on findings from our pilot study, using the software G*Power, version 3.13 (Faul et al. 2007), and assuming two-sided tests with Alpha = .05 and Beta = 0.2 (Power = 0.8). Hypotheses H-1.1 and H-1.2 assuming changes in the subjective and physiological state due to the exposure to the thin ideal correspond to the main effect experimental condition on pre-post exp.-differences. In the pilot study these changes were moderate to large for the subjective states (affect, body image). Assuming such an effect size in the population (*Cohen*’*s f* > 0.30, which can be computed from ɳ^*2*^) the required sample size would be 90, (45 in each condition) to ensure a power > .80. Changes in the physiological variables were small in the pilot study (*f* < .16) and would require a larger sample size of at least 309 participants. However, the experimental manipulation is further qualified. H-1.2 predicts that effects of the thin ideal induction are stronger for patients than for non-patients. This is indicated by an interaction effect (group * condition; contrast: healthy vs. patients), which was small in the pilot study (*f* < .18). Thus the total sample size should be at least 245. H-1.3 predicts differences between the clinical groups and indicated by an interaction effect too (group * condition; contrast: BN + AN vs. clinical control). Due to the rather small number of patients in the pilot study, different diagnostic groups were not compared to each other. Differences between patients with eating disorders and the clinical comparison group are assumed to be small to moderate and thus sample requirements will be similar. With a sample of size of N = 250 also small to medium moderator effects (H-1.4) (Figure 1) could be detected.

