To obtain the required number of 150 patients, taking into account a participation rate of 50% and a dropout rate of 30% in the patient population, a total of 390 patients (c. 130 in each patient group) have to enter the clinical units during the two years of assessment. Thus the recruitment of 195 patients will cover two consecutive years and will be continuous to prevent seasonal effects. In order to achieve the sample size suggested by the power analysis, a sample of 100 healthy controls in Fribourg (50 university students and 50 students of professional schools) is recruited.

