### Randomization

All participants who meet criteria and who give informed consent are randomized to the experimental condition (exposure to fashion magazines) or control condition (exposure to neutral magazines) based on the randomized block/split-plot design approach (Lane 2008). Randomization is performed at the study center at the Department of Psychology in Fribourg. The randomization is stratified by age. The allocation ratio between the two conditions is 1:1.

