### Monitoring and data management

Data will continuously be monitored for completeness, consistency and plausibility by each of the study centers in Bochum, Germany and Fribourg, Switzerland under the lead of the main study center in Fribourg. Data entry will be double-checked. Data quality is ensured based examination of ranges. Data on longitudinal effects will only be released after study completion (after experiment 2). Besides the cross-sectional data no preliminary analysis of the longitudinal data is planned. Study data will be reported in accordance to the Consort guidelines (Moher et al. 2001).

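### Group findings are promised to each woman after her own second session while others are still to be tested, which risks expectancy bias in self-rated primary outcomes

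*Protocol article*

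**What the plan says.** Three parts of the Protocol article bear on this.

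- **Disclosure and debriefing.** Participants enter under a cover story: they are told that the study concerns well-being and bodily responses to everyday stress in young women. After the experiment they are asked not to reveal its purpose to potential participants. Debriefing follows three months later, after the second session, when they "receive a summary of the overall study aim together with preliminary findings" and an overview of their own data.
- **Power analysis.** For patients, "the recruitment of 195 patients will cover two consecutive years and will be continuous".
- **Monitoring and data management.** "Data on longitudinal effects will only be released after study completion (after experiment 2"), and then: "Besides the cross-sectional data no preliminary analysis of the longitudinal data is planned". Longitudinal results are held back. The T1 data are excepted, with no statement of when they may first be compared by exposure condition.

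**The concern.** The debriefing is tied to each woman's own calendar, while recruitment is rolling. Her own second session is protected, because she is told only afterwards. The sessions of other women are not.

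This matters more here than in most trials. The magazine is in plain view, so a participant cannot be blind to her condition. What shields her ratings is that she does not know what response is expected. The primary outcomes (body image, affect, eating behaviour) are self-ratings before and after exposure. A woman who has heard that the fashion magazine made earlier participants feel worse about their bodies may rate herself accordingly. An experimenter who knows an interim result may also convey it. Later participants come from the same clinical units and, among the healthy controls, from Fribourg students, including psychology students. Contamination of this kind cannot be removed in the analysis.

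**Working it through.** **1. What the sample size assumes.** The Power analysis section works "assuming two-sided tests with Alpha = .05 and Beta = 0.2 (Power = 0.8"). For the group-by-condition contrast the effect is one "which was small in the pilot study (*f* < .18"), and the conclusion is "Thus the total sample size should be at least 245". A 1-df F test with noncentrality f²N, α = .05 and power .80 gives N = 245 at f = .18, 90 at f = .30 and 309 at f = .16. All three match the document. As a hand check for f = .18, with d = 2f = 0.36 and the stated 1:1 allocation: n per arm = 2(1.960 + 0.842)²/0.36² ≈ 121.1, so 122, and N = 244. The figures are therefore those of a single fixed-size test. Nothing in them provides for an early look or schedules one.

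**2. When the first findings fall due.** The Procedure section puts the sessions in weeks 3 and 14 of a participant's schedule, a gap of 14 − 3 = 11 weeks. Take patient enrolment as uniform over two years, 104 weeks (an assumption). When the first woman finishes her second session, at about week 14, those who entered within 11 weeks of her have had T1:

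- 11/104 = 10.6%, so about 89% of patients have not yet been tested at all.
- If three months is read as 13 weeks, 13/104 = 12.5%, so about 87% to 88% have not.
- Debriefing and enrolment then overlap for about 104 − 14 = 90 weeks.

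No recruitment period is given for healthy controls, so these fractions cannot be carried over to them.

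**3. What the findings could consist of.** Longitudinal effects are embargoed until completion. Findings handed out during enrolment could then come from (a) accumulating T1 data, which the monitoring section does not bar from preliminary analysis, or (b) the pilot study, whose changes in affect and body image the Power analysis section describes as moderate to large. Either source tells a woman which response is expected.

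**4. What stands in the way.** The request not to reveal the purpose is made after the experiment. The text does not say that it is repeated at debriefing or that it covers findings. No statement keeps interim results from experimenters.

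**5. Size of the bias.** If a share p of women in one condition hears the findings and their ratings shift by δ on average, that condition's mean moves by pδ. The document gives neither p nor δ, so no figure can be put on it.

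**The case against.** The wording allows milder readings. The findings summary carries no date of its own and might be sent later than the debriefing. It might hold only pilot results. The exception for cross-sectional data may mean simply that T1 is analysed once, before T2 is complete, which fits the separate time-point analyses allowed in the Data analytic plan. These readings are possible, but the text does not settle on any of them. The debriefing and the summary stand in one sentence tied to the second session, and pilot results would also reveal the expected response.

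The experimenter route is weaker than the participant route. The experimenter leaves during exposure, questionnaires are computerised and completed alone, and experimenters have no academic or therapeutic tie to participants. These points limit experimenter influence. They do not stop participants from talking to one another.

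It is also fair that the study aim, disclosed at the same debriefing, already breaks the cover story. Delaying group findings therefore closes only part of the leak.

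A reader might go further and infer that repeated T1 analyses inflate the type I error. The document does not support that. It schedules no looks and has no stopping or re-sizing rule. With a fixed sample and one final test, α stays at .05 however often T1 data are summarised. It would rise only if an early look were itself used as the test, and nothing says it will be.

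**Conclusion.** The point holds as a risk of expectancy bias created by the timing of disclosure. On the natural reading, group findings become available from about week 14 of a two-year patient enrolment, with roughly 87% to 89% of patients still to have their first session if enrolment is uniform. The existing request for non-disclosure is a partial safeguard. The magnitude of any bias is unknown, and its likeliest direction is towards the hypotheses.

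The conclusion rests on debriefing following each woman's own second session, and on some contact between earlier and later participants. The timing argument is firm for patients. For healthy controls it depends on a recruitment period that the document does not give. It does not show that findings will in fact be drawn from incomplete T1 data, or that the stated significance level is compromised.

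**What to change.** **Disclosure and debriefing.** Keep the individual debriefing and the personal data overview after session 2. At that point repeat the non-disclosure request and extend it to any findings. Send group findings, pilot results included, only after the last participant's second session. The last second session is the right marker because women between their two sessions can be influenced too.

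**Monitoring and data management.** State that no comparison by exposure condition is made until the last T1 session is complete and the T1 data are locked. This also keeps interim results from experimenters during T1 testing, and it rules out any question of an early look.

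**Cost.** A few sentences and a later mailing. Early participants wait longer for the overall results, and T1 results cannot be presented during enrolment. Because the study aim is still disclosed at individual debriefing, some leakage risk remains.

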### Measures

#### Primary and secondary outcomes

Primary outcome is the impact of thin ideal exposure on body image, affect and eating behavior (for an overview and psychometric properties of interviews and questionnaires, refer to Table 1). The effect of exposure and subsequent TSF induction will be determined by self-rating, visual analogue scales questionnaires (VAS_B, FRS, threeAS, VAS_E).

Secondary outcomes include the psychophysiological stress response induced by thin ideal exposure which is assessed by salivary concentrations of cortisol, alpha-amylase and heart rate (HR) and heart rate variability (HRV).

### Moderators

The ER index includes the capability to decode emotional facial expressions (decode_EMO) self-reported correlates of impulsivity (BIS-15), ER strategies (DERS) measured prior to the experiment and of physiological markers such as (HR and HRV) measured during the whole laboratory waiting room design. Cognitive factors are assessed by the trait variable “thought shape fusion” TSFtrait_B, and the intensity of TSFstate_B.

### Covariates

Depending on the specific hypothesis, analyses will be adjusted for covariates: baseline values of depression (BDI-II) and anxiety (BAI); eating disorder pathology (EDE-Q, DEBQ); socio-economic status, (SES); BMI, internalization of thin ideal (SATAQ-G); trait and correlates of acute appearance schema activation (ASI-R); SSD symptoms (SOMS) self-esteem (RSES), presence of comorbid mental disorders (DIPS). We will further take into account the role of Social Comparison Processes (PACS) and Third-Person Perception (TPP), which has been shown to influence the effects of media exposure in healthy young individuals in media psychology research.

### Methodological aspects

#### Power analysis

Sample size calculations are based on findings of small to medium effects of mass media engagement on body image in young adults from the general population (Levine & Murnen 2009) and based on findings from our pilot study, using the software G*Power, version 3.13 (Faul et al. 2007), and assuming two-sided tests with Alpha = .05 and Beta = 0.2 (Power = 0.8). Hypotheses H-1.1 and H-1.2 assuming changes in the subjective and physiological state due to the exposure to the thin ideal correspond to the main effect experimental condition on pre-post exp.-differences. In the pilot study these changes were moderate to large for the subjective states (affect, body image). Assuming such an effect size in the population (*Cohen*’*s f* > 0.30, which can be computed from ɳ^*2*^) the required sample size would be 90, (45 in each condition) to ensure a power > .80. Changes in the physiological variables were small in the pilot study (*f* < .16) and would require a larger sample size of at least 309 participants. However, the experimental manipulation is further qualified. H-1.2 predicts that effects of the thin ideal induction are stronger for patients than for non-patients. This is indicated by an interaction effect (group * condition; contrast: healthy vs. patients), which was small in the pilot study (*f* < .18). Thus the total sample size should be at least 245. H-1.3 predicts differences between the clinical groups and indicated by an interaction effect too (group * condition; contrast: BN + AN vs. clinical control). Due to the rather small number of patients in the pilot study, different diagnostic groups were not compared to each other. Differences between patients with eating disorders and the clinical comparison group are assumed to be small to moderate and thus sample requirements will be similar. With a sample of size of N = 250 also small to medium moderator effects (H-1.4) (Figure 1) could be detected.

To obtain the required number of 150 patients, taking into account a participation rate of 50% and a dropout rate of 30% in the patient population, a total of 390 patients (c. 130 in each patient group) have to enter the clinical units during the two years of assessment. Thus the recruitment of 195 patients will cover two consecutive years and will be continuous to prevent seasonal effects. In order to achieve the sample size suggested by the power analysis, a sample of 100 healthy controls in Fribourg (50 university students and 50 students of professional schools) is recruited.

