### Participants

Altogether 250 participants will be included in the study. Healthy participants (N = 100) as well as participants suffering from AN (N = 50), BN (N = 50) or mixed mental disorders (depressive, SSD and anxiety disorders; N = 50) will be randomly distributed to either a thin ideal or neutral exposition based on magazine viewing (Figure 2). All participants will be evaluated regarding the presence of any mental disorder during face to face interview based on the Structured Clinical Interview for mental disorders currently adapted for DSM-5 by the [name] group, DIPS for DSM-5 (see Table 1 for an overview of all interviews and psychological questionnaires).

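### The sample requirement for H-1.3 is called similar to 245, but only the 150 patients inform that contrast; at f = .18 power is about 54% (59% at most), not 80%

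*Protocol article*

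**What the plan says.** The Power analysis section of the protocol works with two-sided tests, alpha .05 and power .80. It gives three pairs of effect size and sample size: f = .30 with 90 participants, f = .16 with 309, and f = .18 with 245. The last pair belongs to H-1.2, the group by condition interaction that sets healthy women against all patients, and ends: "Thus the total sample size should be at least 245".

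H-1.3 is then defined as another interaction, "group * condition; contrast: BN + AN vs. clinical control". The section explains that the pilot had too few patients for diagnostic groups to be compared. It gives no f for H-1.3 and says only that these differences "are assumed to be small to moderate and thus sample requirements will be similar".

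The Participants section sets the group sizes: 100 healthy women and "participants suffering from AN (N = 50), BN (N = 50) or mixed mental disorders (depressive, SSD and anxiety disorders; N = 50". That makes 150 patients, 100 with an eating disorder and 50 clinical controls. The paragraph after the power analysis repeats the 150. It assumes 50% participation and 30% dropout, and plans to recruit 195 patients. The Randomization section allocates 1:1 to the two magazine conditions.

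**The concern.** The figure of 245 was obtained for a contrast in which every participant counts. The H-1.3 contrast gives the healthy women zero weight; their only possible contribution is residual degrees of freedom. If the requirement really is similar to 245, patients alone must meet it, and the plan has 150 of them, unevenly split. A reader of the power section would nevertheless conclude that N = 250 covers H-1.3.

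This hypothesis carries the specificity question. The Discussion section says that comparing eating disorders with other clinical conditions will show whether body image disturbance is a general feature of psychopathology or is most pronounced in eating disorders. If the power is believed to be 80% and is in fact well below that, a non-significant H-1.3 could be taken as support for the general-feature reading when the trial had a large chance of missing the effect.

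**Working it through.** **Inputs.** Alpha .05 two-sided, power .80, f = .18 and N = 245 for H-1.2 (Power analysis); 50 AN, 50 BN and 50 mixed disorders (Participants); 1:1 allocation (Randomization); 195 patients recruited and 30% dropout (paragraph after the power analysis). For H-1.3, f is an assumption: .18 is what a requirement similar to 245 implies, and .20 and .25 are shown as a range.

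**Method.** Fixed-effects ANOVA F test with 1 numerator degree of freedom, denominator degrees of freedom N minus the number of cells, and noncentrality λ = f² × N.

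**Reproducing the plan's figures.** The smallest N with at least 80% power is 90 for f = .30, 309 for f = .16 and 245 for f = .18. All three match exactly. For f = .18, 245 participants give 80.1%.

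**H-1.3 with 150 patients at f = .18.**

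- f taken as realised in the 150: λ = .18² × 150 = 4.86, power 59.1%.
- With the 100:50 split, the cells are 50, 50, 25 and 25. In a balanced two-by-two layout, f = .18 corresponds to a difference of differences of 4 × .18 = .72 SD. Its variance here is 1/50 + 1/50 + 1/25 + 1/25 = .12, so λ = .72² / .12 = 4.32 and power is 54.2%. Equivalently, λ is multiplied by 4 × (2/3) × (1/3) = 8/9.
- Taking the error degrees of freedom from all 250 participants changes these to 59.3% and 54.4%. That is all the healthy women contribute.

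**What 80% would take.** At f = .18, 245 patients, or 275 with the 2:1 split. With 150 patients, the smallest detectable f is about .23, or about .245 with the 2:1 split.

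**Range over f and the number of patients.** In each pair, the lower figure uses the 2:1 split and the higher figure takes f as realised in the sample.

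| Patients | f = .18 | f = .20 | f = .25 |
|---|---|---|---|
| 150 | 54–59% | 63–68% | 82–86% |
| 195 | 66–71% | – | – |
| 136 | 50–55% | – | – |

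The 195 row applies if all recruited patients are tested at T1. The 136 row is 195 × 0.7 = 136.5, rounded down, and applies if the 30% dropout falls between T1 and T2. H-1.3 is stated for both time points, and the protocol does not say when dropout occurs.

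**The case against.** The strongest objection is that no f is stated for H-1.3. The H-1.2 interaction is called small, whereas H-1.3 is called small to moderate, which reaches higher. At f = .25, 150 patients are enough (82–86%). This stands, and every power figure here is conditional on f. It does not rescue the sentence in the plan: if f is .25, the requirement is no longer similar to 245; if it is similar to 245, 150 is too few.

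A second objection is that f = .18 could be defined over all 250 participants, which gives 81% power. That corresponds to .18 × √(250/150) = .23 within the patients. It is a larger effect than the one used for H-1.2, and the pilot offers no estimate to support it.

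A third is that baseline adjustment and the planned linear mixed models may add power. They may, but the 245 takes no credit for them either, so the comparison is like with like.

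Two stronger readings are tempting and should not be drawn. First, a reader might treat the power figures as upper limits because the pilot value is given as f below .18. That bound belongs to healthy versus patients. The pilot made no comparison between diagnostic groups, so no bound exists for H-1.3. Second, a reader might count the physiological outcomes as the same error, since the section says they "would require a larger sample size of at least 309 participants" while 250 are planned. The protocol states that requirement openly, makes these outcomes secondary, and nowhere claims 80% power for them, so nothing there is contradicted.

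**Conclusion.** The sentence on H-1.3 is wrong as written. A requirement similar to 245 is not met by 150 patients split 100:50. This structural point needs no particular f.

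The size of the shortfall does depend on f. At the implied f = .18, power with 150 patients is about 54% with the actual split (59% at most), so an effect of that size would be missed in more than 40% of such trials. The figure would be better if up to 195 patients are tested at T1 and worse if about 136 remain at T2. It would not be accurate to say flatly that H-1.3 has 54% power, because the documents fix neither f nor the timing of dropout.

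The correction should be made, but it is not critical: no randomisation, outcome or analysis step is affected, and the three stated pairs of effect size and sample size are themselves correct.

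**What to change.** In the Power analysis section, delete the clause saying that sample requirements will be similar. Put in its place: H-1.3 rests on the patients only (100 with AN or BN, 50 clinical controls); 150 patients give 80% power for f of about .245 or more, and about 54% at f = .18.

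Add one sentence: H-1.3 will be reported with its confidence interval, and a non-significant result will not be read as showing no difference between the clinical groups.

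The cost is two or three sentences and a less favourable stated figure. No additional enrolment and no change of design or analysis are needed.

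### The dropout allowance multiplies by 1.3 instead of dividing by 0.7, so 195 recruited patients leave about 137 after the stated 30% loss, not the required 150

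*Protocol article*

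**What the plan says.** The recruitment paragraph of the Power analysis section in the protocol article sets its aim with the words "To obtain the required number of 150 patients". It then names two losses and the number of admissions that they imply: "taking into account a participation rate of 50% and a dropout rate of 30% in the patient population, a total of 390 patients", about 130 per patient group, must come into the clinics. The next sentence continues: "Thus the recruitment of 195 patients will cover two consecutive years". To these it adds 100 healthy controls, for whom it gives no dropout figure.

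The paragraph before it derives the sample size. For the group-by-condition interaction of hypothesis 1.2 (healthy versus patients) it concludes: "Thus the total sample size should be at least 245". It then works with a total of 250, which is 150 patients plus 100 controls.

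The Participants section gives the same total as the number entering the study, "Altogether 250 participants will be included in the study", made up of 100 healthy women and 50 each with anorexia nervosa, bulimia nervosa and mixed mental disorders. It says that these participants are randomly allocated to the two magazine conditions.

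**The concern.** The dropout percentage applies to the people recruited, so the number to recruit is the number required divided by the proportion retained. Adding 30% of the required number on top is a common slip, and it always under-recruits. If it was made here, the recruitment target does not deliver the patient number that the same sentence says it is meant to deliver.

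Hypotheses 1.2 and 1.3 both make predictions for T2, three months after the first experiment, so the number who remain matters. The 195 and 390 are also operational figures: they tell the clinics how many admissions are needed and when recruitment may stop.

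**Working it through.** **Inputs (Power analysis section).** Required patients 150; participation 50%; patient dropout 30%; 390 entering; 195 recruited; 100 controls; minimum total 245; f = .18 for the hypothesis 1.2 interaction (the article says that the pilot effect was below this); two-sided alpha .05; power .80.

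**1. Reproduce the stated figures.**
- 150 × (1 + 0.30) = 195
- 195 / 0.50 = 390, and 390 / 3 = 130 per patient group

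All three stated figures are matched exactly, so the method was multiplication by 1.3.

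**2. Apply the stated rates forwards.**
- 390 × 0.50 = 195 recruited
- 195 × (1 − 0.30) = 136.5, about 137 patients remaining
- Shortfall: 150 − 136.5 = 13.5, or 9% of the patient target
- Dropout at which 195 would give 150: 1 − 150/195 = 23.1%

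**3. Invert correctly.**
- 150 / 0.70 = 214.3, so 215 recruited
- 215 / 0.50 = 430 entering (428.6, or 429, without rounding in between)
- 430 / 3 = about 143 per patient group
- Check: 215 × 0.70 = 150.5

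**4. Total remaining.** 136.5 + 100 = 236.5, about 237, if no control is lost. This is below 245 and 250.

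**5. Power for hypothesis 1.2.** I used a noncentral F test with 1 numerator degree of freedom and noncentrality N × f². It reproduces the article's three sample sizes: 90 at f = .30, 309 at f = .16 and 245 at f = .18. For unequal patient and control groups with proportions p and q, I multiplied the noncentrality by 4pq.

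| Patients + controls | Total | 4pq | Power, equal groups | Power, actual split |
|---|---|---|---|---|
| 150 + 100 (planned) | 250 | 0.960 | 0.809 | 0.793 |
| 137 + 100 (after 30% loss from 195) | 237 | 0.976 | 0.788 | 0.778 |
| 195 + 100 (no loss before T1) | 295 | 0.896 | 0.869 | 0.831 |

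Compared like for like, the error costs 0.809 − 0.788 = 0.021 on the equal-group basis and 0.793 − 0.778 = 0.015 on the actual split.

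**6. Compare the two sections.** Participants has 150 patients included and randomised. The recruitment paragraph has 195 patients recruited, and the Randomization section randomises everyone who is eligible and consents, which implies 195 + 100 = 295. Both cannot be the number randomised.

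**The case against.** The strongest reply is that the slip hardly matters, and much of that reply stands.

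- **Timing of dropout.** The article does not say when the 30% is lost. The minimum of 245 is for a contrast on pre-to-post exposure differences, which can be estimated at T1 alone, and the Data analytic plan allows the two time points to be analysed separately. If patients leave during the three treatment months, T1 could have up to 295 participants and power above .80. A reader might infer that the trial as a whole misses its minimum of 245. The article supports that only for those who remain after dropout.
- **Partial data.** Linear mixed models are specified partly because of dropout, so patients with only the first experiment still contribute.
- **Size.** The loss in power is about two percentage points. Part of the gap below .80 comes from the 150:100 split, which gives 0.793 even at the full 250.

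Three further inferences should not be drawn. First, taking 250 as the number randomised would leave 150 × 0.70 + 100 = 205 at T2, with power of about 0.73. The recruitment paragraph, however, makes 150 the number wanted after the dropout allowance, so this shows an ambiguity between sections and is not the size of the arithmetic error. Second, hypothesis 1.3 (eating disorders versus clinical controls) has power of only about 0.54 with 150 patients if f = .18 is assumed, and 0.50 with 136. That weakness is largely separate, and the article gives no pilot effect for that contrast. Third, the article limits its 30% to patients. The absence of a control dropout rate is not an arithmetic error, although any control loss would lower the 237 further.

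None of this rescues the stated figures. No other reading of the inputs gives 195 and 390.

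**Conclusion.** The point holds as an arithmetic error with modest consequences. On the article's own rates, 195 recruited patients yield about 137, some 13 short of 150, and about 237 participants in total remain after dropout, against a stated minimum of 245. Power for hypothesis 1.2 in those remaining is about 0.79, or 0.78 with the actual split.

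This rests on the stated 50% and 30%, on no loss among the 100 controls, and on f = .18 as the true effect. If dropout occurs between the two experiments, the shortfall concerns T2 completers only. It should be corrected because the recruitment target contradicts its stated purpose; it does not invalidate the design or the analysis.

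**What to change.** Choose one of two corrections in the recruitment paragraph:

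- State 215 patients recruited and about 430 entering the units, about 143 per patient group, to obtain 150 after dropout. This costs 20 more recruited patients (215 − 195) and about 40 more admissions (430 − 390).
- Keep 195 and 390, and state the true expected yield: about 137 patients and at most about 237 participants after dropout, with the corresponding T2 power of 0.79 (0.78 with the actual split) for hypothesis 1.2 at f = .18. This costs wording only.

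In the same edit, reconcile the Participants section with the recruitment paragraph: say whether 250 (150 patients) is the number randomised or the number expected to remain, and how it relates to the 195 recruited. It would help to say when the 30% dropout is expected. A stated assumption about control loss would also be useful, but is optional.
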